#### Mindfulness practice

Participants will be asked to report their previous experiences with mindfulness-related practices (e.g., meditation and yoga) as well as their ongoing mindfulness practices (both formal mindfulness practices, e.g., meditation on deep breathing, and informal mindfulness practices) in an interview using the TLFB format. This procedure has been used in previous mindfulness-based intervention studies [47].

#### Perceived stress

The Perceived Stress Scale (PSS-4) [9, 59, 60] is a validated and economic four-item self-report scale to measure perceived stress. The items focus on feelings of subjective control or being overburdened (e.g., “In the last month, how often have you felt difficulties were piling up so high that you could not overcome them?”).

#### Emotion regulation

Participants’ emotion regulation will be measured by two assessment tools, the Difficulties in Emotion Regulation Scale (DERS) [61] and *Heidelberger Fragebogen zur Erfassung von Emotionsregulationsstrategien* (H-FERST) [62]. DERS is a 36-item measure. It has been validated in an adolescent community sample and its internal consistency is good. It consists of six subscales (strategies, non-acceptance, impulse, goals, awareness, and clarity) and has shown good internal consistency (Cronbach alpha between .76 and .89) in community samples. H-FERST is a more clinically oriented 39-item self-report measure, which showed good reliability. It consists of nine subscales: rumination, reappraisal, acceptance, problem-solving, suppression of emotional expression, suppression of emotional experience, avoidance, activity/social support, and distraction.

#### Impulsivity

We will use the UPPS impulsive behavior scale as a measure of impulsivity [63], UPPS is an acronym for the scale's targeted concepts urgency, (lack of) premeditation, (lack of) perseverance, and sensation seeking [64]. It has good internal consistency (Cronbach’s alpha = .87) and has been validated.

### Further measures for wider use in the consortium

Several assessments integrated into this study will be used to answer the research questions of the whole IMAC-Mind consortium.

#### Prenatal androgen exposure

Maternal stress and substance use during pregnancy are associated with increased prenatal sex hormone exposure, which is linked to reduced self-regulation and increased psychiatric problems and SUDs in the resulting offspring [65–68]. Prenatal assessment of androgen exposure is difficult, but in various studies, the ratio of the lengths of the second and fourth fingers (2D:4D) has successfully been used as a proxy of intrauterine exposure to gonadal steroids. A low 2D:4D ratio indicates a higher level of prenatal androgen exposure [69] and lower self-regulatory competence in later life. The 2D:4D ratios of the participants, therefore, will be used as a proxy of the adolescents’ disposition to self-regulatory competences, which in turn are associated with SUDs. Participants’ hands will be scanned, and their finger lengths will be measured to obtain the 2D:4D finger length ratio.

#### Neuropsychological testing

A neuropsychological test battery will be integrated into the study to measure participants’ impulsivity, decision-making, reward processing, and risk-taking behavior, all of which have been linked to substance use in adolescents [70]. Three established tasks will be applied: a monetary incentive delay task [71], a stop signal task [72], and the Cambridge gambling task [70].

### Adherence to mindfulness concepts and the quality of intervention delivery

We aim to record sessions on video and evaluate a proportion of mindfulness-based group intervention sessions, from which randomly chosen 20-min intervals are drawn to assess the quality of intervention delivery. Two target variables are assessed independently using the videos: adherence to the standard for mindfulness-based interventions for SUD patients and the competence of the interventionist.

Fidelity to the mindfulness-based interventions will be rated on the Mindfulness Based Relapse Prevention Adherence and Competence Scale (MBRP-AC), which was originally designed for the MBRP program developed by Chawla and colleagues [73]. It has good validity and inter-rater reliability. As our current intervention resembles that program, we felt the items were suitable for the context of this study, too.

The competence of the interventionist, which is independent of mindfulness, is rated with items 1–5 of the Enhancing Assessment of Common Therapeutic Factors (ENACT) scale developed by Kohrt and colleagues [74]. The selected items assess the therapists’ communications skills, rapport building, and empathy. The scale assesses a therapist’s competence for supervision and training and showed good psychometric accuracy.

At least two researchers, with a background in mindfulness-based interventions and therapeutic competence, will independently rate the recorded sessions using both scales (MBRP-AC and ENACT). Inter-rater congruency will be calculated and documented. Each study center (Hamm and Hamburg) will continuously monitor intervention delivery in the other center using the video recordings.

### Intervention feasibility

The interventionists will assess their perception of the feasibility of the mindfulness-based group intervention using the Structured Assessment of Feasibility (SAFE) [75] after the final session. This scale has good inter-rater reliability (*k* = .84) and test–retest reliability (*k* = .89).

### Safety

A set of adverse events (AEs) and serious adverse events (SAEs) were defined and their prevalence and any possible causal relation to the new mindfulness-based group intervention under evaluation were tracked. All AEs and SAEs, from the first mindfulness-based group intervention to 28 days after the last mindfulness-based group intervention, will be documented in the patient’s file. Each AE and SAE will continue to be monitored until the event has terminated and the participant’s state has improved or at least proved to be stable but no longer than 3 months after the end of the participant’s treatment. The study team will evaluate any possible causal relationship between AEs and SAEs and participation in the mindfulness-based group intervention and documents this.

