**Discussion:**

This trial is expected to provide evidence of the added effect of a novel, safe, and feasible treatment option for adolescents with SUD.

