### Methods against bias

The study follows the CONSORT statement for randomized controlled trials [40]. This includes the publication of a study protocol and the study’s public registration (German Register of Clinical Studies, DRKS00014041). The procedures for study inclusion and assessment (obtaining informed consent, handling of questionnaires, clinical records, and clinical interviews) are performed by study personnel who remain blind to the participants’ randomization to either the intervention group (mindfulness-based group intervention “Mind it!”) or the control group (treatment as usual) and who are not involved in providing treatment. Blinding of patients is not possible due to their (non-)participation in the mindfulness-based group intervention. Self-reports regarding substance use are validated through urinalyses, which are routinely taken as part of SUD treatment and are extracted from medical records. Diagnostic assessments are based on highly standardized measurement tools and clinical information is provided by experienced clinicians. All study personnel are trained to conform to current guidelines and regulations (e.g., data safety). Questionnaire data will be computerized by trained staff using the EpiData software to ensure the high quality of the entered data. Additionally, a clinical research organization will monitor adherence to the study protocol and overall study quality. A data and safety monitoring board will oversee study procedures, recruitment, and data flow twice yearly and advise project staff when necessary.

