### Procedure

The procedures in the current study have been approved by the ethics board of Ruhr University Bochum (176268). During participant recruitment and treatment, two study centers (Hamm and Hamburg; Hamm is the coordinating center) will provide a mindfulness-based group intervention in addition to what is routinely provided as standard inpatient SUD treatment. Patients admitted to either study center because of SUD treatment and who have completed detoxification are given information about the study and their possible participation if they are eligible for study participation according to the inclusion and exclusion criteria. After written informed consent is given by both the patient and their parent or guardian, the *t*_0_ assessment will be performed within 1 week after the transition from detoxification treatment to after-detoxification treatment. After the *t*_0_ assessment, patients will be randomized to either the intervention group (mindfulness-based group intervention in addition to standard treatment) or the control group (standard treatment as usual). The patients will be randomly allocated to either the Mind It! group or the control group in a 1:1 allocation ratio, stratified by study center with variable block lengths. The randomization lists will be prepared by the Department of Medical Biometry and Epidemiology of the University Medical Center Hamburg-Eppendorf. The central allocation procedure is managed by the coordinating study center in Hamm to guarantee allocation concealment.

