The intervention group receives a mindfulness-based group intervention consisting of 12 45-min sessions relating mindfulness techniques to substance use problems in adolescents. In each of the first 4 weeks of the intervention, the participants receive two 45-min sessions of the core mindfulness-based group intervention. At the end of the 4 weeks, they undergo the first interim assessment (*t*_1_). In weeks 5–8 of treatment, intervention group participants receive one weekly 45-min session of the sustained mindfulness-based group intervention (maximum of four sessions). After the total mindfulness-based group intervention and after 8 weeks of treatment, participants undergo another assessment (*t*_2_), which is followed by the final assessment (*t*_3_) 6 months after *t*_2_. Assessments for *t*_3_ are performed by study personnel and participants receive €50 and travel expenses as compensation for participation in the *t*_3_ assessment. The mindfulness-based group intervention is delivered by clinically experienced researchers, who are currently in therapeutic training or have finalized therapeutic training, and are experienced in giving mindfulness-based interventions. Figure 2 gives an overview of the study flow.

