### Analyses

Data will be analyzed according to the CONSORT statement [40]. A detailed statistical analysis plan will be prepared and finalized before breaking the blind. Descriptive statistics will be determined for the intention-to-treat population according to treatment assignment. The intention-to-treat population consists of all randomized patients. The primary hypothesis is that the intervention is superior to treatment as usual according to the number of days with substance use within the past 30 days 6 months after the end of the intervention (*t*_3_). A mixed negative binomial regression will be performed based on the intention-to-treat population with treatment group, time, interaction between treatment group and time, and recruitment center as fixed effects, the number of days with substance use within the past 30 days at baseline as a covariate, and patient and therapy group as random effects. The contrast of the treatment group at *t*_3_ will be interpreted in a confirmatory manner. We will report adjusted group differences with corresponding 95% confidence intervals and *p* values. Mixed models are more robust against missing values than models without random factors and yield unbiased estimates under the missing at random assumption. For model diagnostics, a systematic examination of factors associated with loss to follow-up will be conducted. Missing values will be imputed in a sensitivity analysis by the multiple imputation method. Additionally, the primary analysis will be conducted on the per protocol population. The following subgroup analyses will be planned. The secondary outcomes will be analyzed in an exploratory manner with appropriate models with the same covariates and fixed and random effects as in the primary analysis. Multiple mediation models for identifying the mechanisms of intervention effects (with a focus on behavioral measurements of self-regulation and mindfulness) will be used [77]. The safety end points will be determined with a mixed logistic regression. Interim analyses are not planned. The two-sided type I error will be set at 5%. Statistical analyses will be carried out with SPSS, Version 21 (IBM Corp., Armonk, NY).

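### Adverse-event recording is defined only by mindfulness sessions, so as written controls have no recording window and the intervention arm's window depends on attendance

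*Protocol article*

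**What the plan says.** The Safety section of the protocol article fixes both ends of the recording period by reference to the intervention: "All AEs and SAEs, from the first mindfulness-based group intervention to 28 days after the last mindfulness-based group intervention, will be documented". It gives no other start or end date for recording. The stated purpose is to follow how often events occur, and "any possible causal relation to the new mindfulness-based group intervention under evaluation were tracked". A recorded event is then followed until it has resolved or stabilised, but "no longer than 3 months after the end of the participant’s treatment".

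The two arms differ in exactly the feature that defines the window. Under Procedure, the comparator is "the control group (standard treatment as usual", without the group sessions. Methods against bias confirms this: "Blinding of patients is not possible due to their (non-)participation in the mindfulness-based group intervention".

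On analysis, the article says only: "The safety end points will be determined with a mixed logistic regression". It does not list the model terms, the coding of events or the population for this model. The abstract's Discussion paragraph expects evidence on a "novel, safe, and feasible treatment option for adolescents with SUD".

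**The concern.** A recording rule tied to sessions cannot be applied to an arm without sessions. Site staff must then improvise for controls: record nothing, record for the 8 weeks of treatment, or record for some other period. Each choice gives a different event count for the same underlying risk.

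The rule is also uneven within the intervention arm. Events between randomisation and the first session fall outside it. A patient who is randomised but never attends has no window, although the intention-to-treat population is defined as all randomised patients. Those who stop attending early are observed for less time than those who complete.

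At stake is the trial's safety statement in patients aged 13 to 19. Relapse and psychiatric events can plausibly occur under standard treatment alone, so judging each event's causality case by case is no substitute for a comparable control rate. Because this is a rule for data collection, a later analysis plan cannot recover events that were never recorded, and the article states that recruitment is under way.

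**Working it through.** **1. The plan's own figures.** The article gives no figure for the safety comparison. Its only sample-size figure is for the primary outcome: d = 0.36, two-sided alpha 0.05 and 80% power. A two-sample t-test calculation gives 122.09, rounded up to 123 per arm and 246 in total, which matches the article. That figure is not in question; 123 per arm is used below only to scale the illustration.

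**2. Window lengths that follow from the rule.** Under Procedure, "In each of the first 4 weeks of the intervention, the participants receive two 45-min sessions of the core mindfulness-based group intervention", followed by one session a week in weeks 5 to 8, at most four.
- Completer: 8 weeks of sessions + 28 days = 56 + 28 = about 84 days (a few days less if the last session falls early in week 8).
- Patient who stops after week 2: 14 + 28 = about 42 days.
- Intervention patient who attends no session: no window.
- Control patient: no window stated.

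**3. What a mismatch could do.** The article gives no event risk and no control window, so the following are assumptions: the true hazard is constant and the same in both arms, events are coded as any versus none, and staff use the 8-week treatment period for controls while intervention patients are observed for 12 weeks.

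With p8 the 8-week risk, the 12-week risk is 1 − (1 − p8)^(12/8), and the odds ratio (OR) is [p12/(1 − p12)] / [p8/(1 − p8)].

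| p8 | p12 | Spurious OR |
|---|---|---|
| 0.10 | 1 − 0.90^1.5 = 0.146 | (0.146/0.854)/(0.10/0.90) = 1.54 |
| 0.20 | 1 − 0.80^1.5 = 0.284 | (0.284/0.716)/(0.20/0.80) = 1.59 |
| 0.30 | 1 − 0.70^1.5 = 0.414 | (0.414/0.586)/(0.30/0.70) = 1.65 |

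**4. The same check anchored on the 84-day risk, with 123 per arm.** The risk over L days is 1 − (1 − p84)^(L/84). The rejection rate is that of a simple two-sided comparison of two proportions at 5%, which ignores the random effects of the mixed model.

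| Intervention / control window | p84 = 10% | p84 = 30% |
|---|---|---|
| 84 / 84 days | OR 1.00, rejection 5% | OR 1.00, rejection 5% |
| 84 / 56 days | 10.0% v 6.8%, OR 1.53, rejection 15% | 30.0% v 21.2%, OR 1.60, rejection 35% |
| 42 / 84 days | 5.1% v 10.0%, OR 0.49, rejection 30% | 16.3% v 30.0%, OR 0.46, rejection 72% |

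The last row is an outer bound, because it supposes that the whole intervention arm stops after week 2. It shows that the sign can reverse: short attendance against a full control window would make the intervention look protective. With equal windows the distortion disappears.

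**The case against.** Several objections carry weight.

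- **The comparison is inferred.** The sentence on the safety model names no contrast between arms, no outcome coding and no handling of exposure. A reader might infer that a between-arm test of any versus no event is planned and is invalid. The document does not say that. An arm comparison is the natural reading of a regression in a two-arm trial whose other models carry treatment group as a fixed effect, but it remains a reading.
- **Silence is not zero observation.** A reader might also infer that controls are not observed for adverse events at all. The article only leaves their window undefined. It speaks of all events, of the patient's file and of the end of treatment, and these terms could apply to either arm. The full protocol may define a control window. This stands as a limit on the claim. It does not remove the point, because the published rule is complete in form and any different rule for controls would have to be reconciled with it.
- **Harm that leads to stopping is mostly captured.** An event that makes a patient stop attending occurs before, or within 28 days of, the last session, so it is generally recorded and followed. What is lost is later events. The suggestion that the rule hides harm-driven dropout is therefore weak.
- **Starting at first exposure is a familiar convention.** That is true for describing events in a treated group. It does not give a comparator a start date.
- **The odds ratios are hypothetical.** This is accepted. A constant hazard is doubtful across day or inpatient treatment and the period after it.
- **Safety is not the confirmatory hypothesis.** This is also accepted, and a data and safety monitoring board reviews the trial twice a year. The t3 contrast on days of substance use is unaffected.

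**Conclusion.** The point holds in limited form. Followed as written, the recording rule yields no window for controls, none for intervention patients who attend no session, and a window that varies with attendance for the rest. This is a stated rule that produces non-comparable data. It is not a detail that can be left to the analysis plan.

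If the safety regression compares the arms, its result is not interpretable unless an arm-neutral window is specified. The size of any distortion cannot be known from the article. The illustrative range of about 1.5 to 1.65 rests on assumed equal constant hazards, an assumed 8-week control window and assumed risks of 10% to 30%; other mismatches push the odds ratio below 1. The documents do not support saying that controls are unobserved, that the comparison is already invalid, or that the intervention will look worse or better than it is.

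**What to change.** Replace the session-based limits with one calendar window for both arms, independent of attendance: from randomisation to 28 days after t2, about 12 weeks. Make the same adverse-event enquiry in both arms at t1 and t2. No visit falls in the 28 days after t2, so cover them in both arms either at the existing t3 visit or by the same record review. Alternatively, end the window at t2 and accept the loss of those 28 days.

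State that the safety model compares the arms, if that is the intention, and analyse all randomised patients over this window. If follow-up is incomplete, use an event-rate model (Poisson or negative binomial with log follow-up time as offset) or a complementary log-log model with that offset. An exposure offset does not have that meaning in a logit model, so adding one to the planned regression would not correct for unequal time.

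The cost is a short amendment and a retrospective record review for controls already enrolled. No extra visits are needed. If the last 28 days are covered at t3, some recall error must be accepted, because that period ends about five months before the visit.

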### Sample size calculation

Based on prior research [29, 31, 32], we expect to detect a small to medium-sized effect of *d* = 0.36 for our primary outcome. We calculated the sample size using G*Power [76], with a two-sided alpha level of 0.05 and a study power of 80%. The required sample will comprise 246 participants (123 both in the control group and in the intervention group). To achieve this sample size, we seek to screen *N* = 340 patients for eligibility for the trial (Fig. 1).

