### Intervention group

The mindfulness-based group intervention under evaluation in this study will be written up as a manual and is based on previous studies on MBCT [26, 41], MBCT for children [42], and MBRP [26–30, 41]. Research has indicated that MBRP can significantly reduce the risk of craving-induced relapses in SUD patients. The current manual will be closely aligned to the existing English-language treatment manual by Himelstein and Saul [43], *Mindfulness-based substance abuse treatment for adolescents*, which was developed in California for incarcerated youth with SUD problems but was later validated in inpatient, outpatient, educational, and community settings as a group intervention [35, 43–45].

The mindfulness-based group intervention integrates both formal mindfulness meditation practices from MBCT (such as body scan meditation, mindfulness of the breath meditation, mindfulness of the body in movement, and sitting meditation) and informal mindfulness practices, which supports participants to integrate mindful awareness into their daily routines. Inquiry is used as a group technique to reflect on experiences during meditation and psycho-education elements are used to teach participants about substance use, stress, stress reactivity, cravings, and coping skills, and they are given a rationale on why mindfulness helps with substance use problems. Each session includes formal mindfulness meditation practice and participants are encouraged to practice mindfulness outside the group sessions.

The group intervention mindfulness practice is adapted to the developmental needs of the young participants regarding duration and content. Therefore, we decided to make group sessions rather short (45 min) but deliver them more often compared with mindfulness-based intervention sessions with adults, such as, for example, MBCT or MBRP. Group sizes will be limited to a maximum of eight participants, so that individual attention can be given to them. Moreover, we plan to integrate simple sensory exercises, movement exercises, and playful activities with significant variation in the mindfulness practice rather than delivering an extended talk. Sessions will include SUD-specific treatment elements from MBRP (such as the identification of possible relapse triggers), mindfulness-based coping skills (such as acceptance), and skills specifically targeting cravings (such as urge surfing) [30].

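### The 80% power for 246 patients assumes independent patients, although the primary model allows for therapy-group clustering that the Mind it! groups create in the intervention arm only

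*Protocol article*

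**What the plan says.** All references are to the protocol article.

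- **Sample size calculation:** "we expect to detect a small to medium-sized effect of *d* = 0.36 for our primary outcome". The calculation was done in G*Power "with a two-sided alpha level of 0.05 and a study power of 80" per cent, and "The required sample will comprise 246 participants (123 both in the control group and in the intervention group"). No cluster size, ICC or design effect is mentioned.
- **Analyses:** the confirmatory contrast at t3 comes from a mixed negative binomial regression with "patient and therapy group as random effects". Baseline days of use is a covariate. A detailed analysis plan is announced for before unblinding.
- **Procedure:** patients are randomized individually "in a 1:1 allocation ratio, stratified by study center with variable block lengths" to "the intervention group (mindfulness-based group intervention in addition to standard treatment) or the control group (standard treatment as usual").
- **Intervention group:** "Group sizes will be limited to a maximum of eight participants".
- **Standard SUD treatment:** both arms receive this care, and its elements are given individually or in groups.

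The article does not define therapy group, and it does not say what value a control patient takes for it.

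**The concern.** Two stated elements of the plan rest on different assumptions. The sample size treats all 246 outcomes as independent. The primary model allows outcomes of patients treated in the same group to be correlated. Patients who share sessions, a therapist and each other's company for eight weeks may well end up more alike than patients drawn at random. If so, the mean of the intervention arm is less precise than 123 independent patients would make it. The control arm has no Mind it! groups, so the design is partially nested: clustering from the intervention acts in one arm only.

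At stake is whether 80% describes the test that will be run. The 246 leaves only 0.3 percentage points of margin, so any real clustering that is not offset elsewhere takes power below the stated level. A null result would then be read against a sensitivity that the trial did not quite have. A later analysis plan can define the model, but it cannot turn a power figure for an independent-patient t-test into the power of that model.

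**Working it through.** **Inputs from the article.** d = 0.36 (so SD = 1), two-sided alpha 0.05, power 80%, 123 per arm, groups of at most 8 in the intervention arm only, baseline days of use as covariate.

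**Assumptions, because the article gives no figures.** ICC 0.01 to 0.10; mean group size m from 4 to 8 (eight is a ceiling, not a mean); baseline-outcome correlation r = 0.3 for illustration. The work stays on the standardized-difference scale that the article uses for its own calculation.

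**Step 1: reproduce 246.** Two-sample t-test, noncentral t, independent patients:

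- 122 per arm: 79.97%
- 123 per arm: 80.29%

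So 123 per arm is the smallest size that reaches 80%, and it contains no allowance for clustering. The normal approximation used below gives 80.6% at 123 per arm, which is the reference for the steps that follow.

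**Step 2: add clustering in the intervention arm.**

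DE = 1 + (m - 1) x ICC; Var(difference) = (DE + 1)/123; power = Phi(0.36/SE - 1.96).

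Example, m = 8 and ICC 0.05: DE = 1 + 7 x 0.05 = 1.35; Var = 2.35/123 = 0.0191; SE = 0.138; 0.36/0.138 = 2.60; power = Phi(0.64) = 74%.

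| ICC (assumed) | m = 4 | m = 6 | m = 8 |
|---|---|---|---|
| 0 | 80.6% | 80.6% | 80.6% |
| 0.01 | 80.0% | 79.6% | 79.2% |
| 0.02 | 79.4% | 78.7% | 77.9% |
| 0.05 | 77.7% | 75.9% | 74.0% |
| 0.10 | 74.9% | 71.4% | 68.1% |

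**Step 3: small-sample degrees of freedom.** With 123/8, or about 15 groups, Satterthwaite degrees of freedom give 77.6%, 72.0% and 65.6% at ICC 0.01, 0.05 and 0.10. With 123/4, or about 31 groups, they give 79.2%, 76.8% and 73.9%. The loss against Step 2 is about 1 to 2.5 points.

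**Step 4: gain from baseline adjustment.** Multiply the variance by 1 - r². At r = 0.3 this is 0.91. At ICC 0.05:

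- m = 8: 0.0191 x 0.91 = 0.0174, SE 0.132, power 77.9%
- m = 6: power 79.7%
- m = 4: power 81.4%

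The r that exactly cancels the clustering at m = 8 and ICC 0.05 solves (1 - r²) x 2.35 = 2, so r = sqrt(1 - 2/2.35) = 0.39.

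**Step 5: detectable effect.** The effect that 246 patients detect with the planned power scales with sqrt((1 + DE)/2). At ICC 0.05, before baseline adjustment: m = 4 gives 0.36 x sqrt(1.075) = 0.37; m = 8 gives 0.36 x sqrt(1.175) = 0.39.

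**The case against.** The strongest reply is that no shortfall has been shown. A random effect in a model allows for correlation; it does not establish that there is any. At ICC 0.01 to 0.02 power is 77.9% to 80.0%, and the baseline covariate, which the sample size also ignores, may recover the difference. Groups may also be smaller than eight. All of this stands. It is why the point is worded as a condition on the 80% and given as a range. It does not remove the mismatch, because the article states neither the ICC nor the baseline correlation on which the condition depends.

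Some stronger readings are tempting, and the article does not support them:

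- **That 80% power is not met.** This needs an ICC that the article does not give.
- **That the random effect is wrong for the control arm.** The article leaves the term undefined for controls; it does not state a wrong rule. Standard treatment also has group elements, so the term may have been meant more widely, and the announced analysis plan can still define it.
- **That power could collapse through coding.** If all controls were entered as one group, the control variance at ICC 0.05 would be 0.95/123 + 0.05 = 0.0577, the SE 0.262 and power about 28%. Nothing in the article proposes that coding.
- **That power falls to about 64% at ICC 0.05 (m = 8) with 20% loss to follow-up.** The 20% is not in the article. That loss alone, without clustering, would bring power to about 71%, so most of the fall is not a clustering effect.

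Nor is there an arithmetic error: 246 follows exactly from its inputs.

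**Conclusion.** The point holds as a mismatch between the sample size and the primary analysis. The 80% is the power of an independent-patient t-test, and it carries over to the planned model only if the therapy-group ICC is near zero or baseline adjustment makes up for it. Against 80%, the unadjusted shortfall is at most about 1 point at ICC 0.01, 2 to 6 points at 0.05 and 5 to 12 points at 0.10, for mean group sizes of 4 to 8. With r = 0.3, ICC 0.05 gives roughly 78% to 81%. The ICC, the mean group size and r are assumptions, and the figures use a normal approximation on the article's own standardized scale rather than the negative binomial model itself. This should be fixed; it is not a must-fix, because the analysis already allows for clustering and the likely loss is modest.

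**What to change.** 1. **Restate what 246 patients deliver.** Give power, or the detectable effect, for a partially nested design over a range of ICCs and mean group sizes, including small-sample degrees of freedom and the expected gain from baseline adjustment. State the assumed ICC and mean group size. As a guide, the detectable effect at ICC 0.05 is about 0.37 to 0.39 before baseline adjustment.
2. **Define the therapy-group term.** In the analysis plan, say that it means the Mind it! group, let its random effect act only in the intervention arm (for example as a random coefficient on the intervention indicator, with no group term for controls), and name a small-sample degrees-of-freedom method such as Satterthwaite.

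The cost is one recalculation and one line of model specification. No extra patients are needed. The stated figure may become slightly less favourable, but a null result could then be judged against the sensitivity of the analysis that was run.
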